### Instrumentation

QT interval was selected for monitoring in this study because it is the ECG element most likely to reflect early acute rejection, as previously noted, and because in the setting of early post-transplantation, it is free of neurologically mediated influences. In the first year after transplantation, the cardiac allograft is denervated [13]. A potential major benefit of allograft denervation in the NEW HEART study is that without the confounding influences of heart rate and autonomic nervous system activity, an observed increase in the QT interval is likely to indicate abnormal ventricular repolarization due to another cause, such as acute allograft rejection.

After a thorough search of the available technology, the HeartView™ ECG Personal Recorder-Transmitter (Aerotel Medical, Israel) was selected. The ECG device records 10 s of the six limb leads (I, II, III, aVR, aVL, aVF) and two precordial leads (V5 and V6 will be used for this study). The HeartView™ device acquires data at a sampling rate of 500 samples per second which is the standard resolution recommended for diagnostic electrocardiography. The device's reliability and validity for ECG diagnosis are evidenced by approval by the U.S. Food & Drug Administration that requires the device to meet criteria stipulated by the Association for the Advancement of Medical Instrumentation for electrocardiograph instruments [14].

The HeartView™ will be used to transmit the subject's ECG to the Core Laboratory at UCSF ("[name] Lab") (Figure 1). Subjects will be given HeartView™ and Internet Transmitter devices (Aerotel Medical, Israel) for the 6-month monitoring period. Once the patient records his ECG, the HeartView™ device will automatically seek, find, and upload the ECG by wireless Bluetooth communication to the Internet Transmitter. Then, using mobile phone technology (subscriber identity module [SIM] card), the Internet Transmitter device will automatically seek, find, and send the digital ECG to a UCSF server via wireless General Packet Radio Services (GPRS) internet access. Thus, subjects do not have to dial a telephone to transmit the ECG, nor do they need to have a home computer or even be computer literate. Subjects need only to record their ECG; the rest will be automatic.

**Figure 1 F1:**
[figure not shown]
**HeartView™ Device and Transmission System**.

### Procedures

Participants will be recruited either while they are in the hospital for transplant surgery, or if that is inconvenient, during their first clinic visit following transplant surgery. After informed consent is obtained, demographic and clinical data will be collected by self-report and by medical record audit. At the time of each EMB, data from the medical record will be abstracted to confirm current medications, serum levels of anti-rejection medications, clinical data regarding EMB results, and other clinical data reflecting myocardial performance consistent with rejection status. Only one anti-rejection medication (tacrolimus) is associated with an increased QT interval. If a patient is on chronic tacrolimus therapy without a change in dosage, it should not interfere with the daily ECG monitoring measurement because we will be comparing each patient with him/herself and noting any change from the previous day's QT interval. However, we will track initiation or change in any QT-prolonging drug. On their website, the Arizona Center for Education and Research on Therapeutics [15] maintains a comprehensive list of QT- prolonging drugs that we have incorporated into the medications section of our electronic database system. Further, on a quarterly basis, we will continue to reference this website for new drugs as they come to market and update our data capture to include those associated with QT-prolongation.

The other drug class that patients may be taking is 3-Hydroxy-3-Methyl-Glutaryl Coenzyme A Reductase inhibitors (i.e., statins) which are known to shorten the QT interval. Thus, we will also monitor statin therapy. To insure patient safety, we will notify patients' transplant cardiologists within 48 h of the detection of any QTc interval exceeding the population 99th percentile for adult males (> 470 ms) or females (> 480 ms) [16].

At the time of informed consent and enrollment, subjects will receive the HeartView™ recorder and its companion Internet Transmitter, which will transmit the subject's ECG as described earlier. Subjects will be asked to record a 10-s 8-lead ECG daily for 6 months.

Participants and their caregivers, if available, will be instructed in the use of the HeartView device using a standardized training booklet. Each enrollee will be given the opportunity to practice transmission and will receive feedback, if needed, prior to the beginning of daily recordings. Daily recordings will be monitored by study personnel to insure quality of transmissions.

Participants will be instructed to make and upload ECG recordings at any time of day that is convenient for them, although they will be urged to select a consistent time to promote adherence to recording. Across participants, a standard recording time is not required because in the early post transplant period complete allograft denervation results in failure of parasympathetic or sympathetic nerves to influence heart rate. In normal individuals at rest, parasympathetic influences via the vagus nerve predominate resulting in a resting heart rate of 60-90 beats/min in adults. However, without such parasympathetic influence on the allograft, transplant recipients experience a permanent tachycardia (99 ± 12 beats/min) and exhibit little heart rate variability over a 24 h period [17]. For the current study, this means that subjects will be able to record their daily ECGs at any time without the confounding influence of 24-h variability on ECG intervals. However, participants will be instructed to wait for at least ten minutes after exercising before recording an ECG. This is necessary because allograft beta receptors are functional early after transplant [17] and respond to increases in circulating catecholamines, such as that elicited by exercise. This post-transplant response to exercise is less immediate than in normal individuals and after cessation of exercise, peak heart rate also recedes at a slower pace, over about a 10-min period [17].

### Analysis of ECG monitoring data

The ECG will be sent to a large server hosted by the UCSF Office of Academic and Administrative Information Systems (OAAIS). The server is a secure, highly redundant data center with 24/7 availability due to back-up generators that protect against power outages. The system provides nightly data backup. Investigators in the [name] Lab will access the ECG data by logging on with a username and password via a Virtual Private Network (VPN), which encapsulates data transfers between networked devices not on the same private network and keeps the transferred data private from other devices. Investigators who analyze the daily ECG data will be blinded from all information regarding the subject's clinical status and biopsy results. In addition, pathologists who grade the biopsies and clinicians who provide medical care in the transplant clinics will be blinded from the QT interval monitoring data.

QT and RR intervals will be made in a computer-assisted manner. The Aerotel measurement software provides a zooming feature to enlarge ECG waveforms for better visualization. In addition, electronic calipers are provided so that the researcher will select the appropriate waveform onset and offset points and the computer software will provide the interval value in milliseconds (ms). The QT interval will be measured from the onset of the QRS waveform to the end of the T waveThe end of the T wave will be defined as the intersection of a tangent to the steepest slope of the last limb of the T wave and the baseline (Figure 2) [18]. A standardized correction to account for the effect of HR will be applied (QT_C_). An increase in the QT_C _interval from the previous day of at least 25 ms that persists for 3 consecutive days will be considered abnormal [10].

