N = 65 Richartz et al. 1998 [8]	Prospective; Rejection during in-hospital period	1. Mean QT_C _= 449 ± 2 ms without rejection; 517 ± 11 ms with rejection (*p *< 0.001) 2. > 10% increase in QT_C _predicted rejection with sensitivity, 86%; specificity, 88%	1. Only observed rejection during hospitalization for transplant surgery 2. Analyzed only 3 ECGs per subject 3. ECG analyzers not blinded from clinical information about rejection	An increase in the QT interval predicts acute allograft rejection

N = 52 Kolasa et al. 2005 [9]	Retrospective; Long-term mortality over 7 yrs	Poorer survival over 7 yrs in subjects who had a > 10 ms per year change in their QT_C _interval on their annual ECG	1. Link to rejection not studied 2. Analyzed only one ECG per year	As little as a 10 ms change in the QT interval is linked to mortality

N = 200 Tenderich et al. 2006 [10]	Retrospective; Rejection during first 3 months	> 25 ms increase in QT_C _interval predicted acute allograft rejection with sensitivity, 77%; specificity, 96%.	1. Only analyzed 2 ECGs per subject 2. ECG analyzers not blinded from clinical information about rejection	Increase in QT interval predicts acute rejection during the period of interest

N = 587 Vrtovec et al. 2006 [11]	Retrospective; Long-term mortality up to 17 yrs	1. Patients with ≥ 10% increase in QT_C _interval between 1^st ^and 2^nd ^year post-transplant had 6.86 times higher risk of dying.2. ≥ 10% increase in QT_C _was the only independent predictor of long- term mortality on multivariate analysis 3. Trend was a decreasing QT_C _over the yrs suggesting sympathetic reinnervation	1. Link to rejection not studied 2. Analyzed only one ECG per year	An increase in the QT interval is linked to mortality

N = 71 Vrtovec et al. 2008 [12]	Retrospective; 1- year all-cause & SCD mortality in subjects with severe acute rejection	1. QT_C _was longer in SCD group than in survivors (475 ± 57 versus 437 ± 36 ms; *p *= 0.02) 2. Patients who had > 10% increase in QT interval during a severe acute rejection episode were at increased risk for SCD.	1. Limited to just patients with severe rejection; unable to tell whether increased QT interval could predict earlier, milder forms of rejection 2. Analyzed just 2 ECGs per subject (one at baseline 7 days after surgery, second at time of rejection)	An increase in the QT interval is linked to mortality

ms = millisecond; SCD = sudden cardiac death; QTc = QT interval corrected for heart rate

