## Methods/design

### Design

The NEW HEART study is a prospective, double-blind, multi-center descriptive research study. The primary aims of the NEW HEART study are to: 1) determine whether an increase in the QT interval during the first 6 months following heart transplant is a sensitive and specific biomarker for acute allograft rejection; 2) determine the timing of initial increased QT interval relative to biopsy-diagnosed stages of mild, moderate, and severe allograft rejection.

Secondary aims are to: 1) determine whether an increase in the QT interval during the first 6 months following heart transplant predicts mortality within the first year, and 2) explore additional ECG measurements that might predict acute allograft rejection or death.

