### Diagnosis of acute allograft rejection

Rates of acute allograft rejection have varied, but the most recent rates of rejection in the first 6 months after transplant are reported to be 25 to 35% [2]. The diagnosis of acute allograft rejection is made by an EMB which will be performed in the hospital cardiac catheterization laboratory at each site. Generally, 3-6 biopsy specimens of the right ventricular endocardium are taken to minimize false negative tests. Each site will follow its own acute rejection surveillance protocol. In general, these protocols require weekly or biweekly EMBs during the first two to three post-transplant months. After that time, biopsies are performed less frequently, based on clinical judgment and risk of rejection. At each site, EMBs will be graded by clinical pathologists experienced with the heart transplant population and using the International Society of Heart and Lung Transplantation standards for acute rejection. Although early reports indicated inter-operator variability in the interpretation of EMB results [22], the use of the standardized grading system has improved the reliability and validity of the measurement. Current variability in interpretation of biopsy results occurs mainly in the diagnosis of Grade 2 rejection by local pathologists which may be misinterpreted in the presence of endocardial infiltrates called Quilty lesions [23,24]. To control for potential variability, we will monitor and record clinical and hemodynamic indicators of myocardial performance, which are obtained at the time of each biopsy or at regular clinical assessments, to support the biopsy interpretation, particularly regarding Grade 2 rejection. Such a multi-factorial approach to identification of rejection has been recommended [24].

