### Statistical analysis

Using the variable definitions in Table 2, a logistic regression analysis will be performed with the independent variable being presence/absence of the ECG criteria (ΔQT_C _≥ +25 ms × 3 days [10]) and the dependent variable being presence/absence of acute allograft rejection. Odds ratios and confidence intervals will be reported as well as the universal proportions used to determine the value of new diagnostic criteria (sensitivity, specificity, positive/negative predictive value, and predictive accuracy, Table 3).

**Table 2 T2:** Variable definitions for statistical analysis

Variable	Definition	Type of Variable
ΔQT_C_	≥ +25 ms increase in QT_C _interval from previous day lasting 3 consecutive days [10]	Continuous (expected range, 10-100 ms)

Acute allograft rejection	EMB category 1R or 2R or 3R with confirmation by treating physician	Categorical; dichotomous (yes/no) No = 0; Yes = 1R or 2R or 3R

Days to rejection	Number of days from first positive ECG criterion to mild, moderate, or severe rejection diagnosis. If the ECG criterion follows rejection, a negative # of days will be reported.	Continuous (expected range -365 to +365)

Acute rejection severity	EMB category: 1R (mild), 2R (moderate), 3R (severe)	Categorical

Cardiac rhythm	Sinus rhythm, atrial fibrillation, atrial flutter, junctional rhythm	Categorical

Heart rate	Heart rate per minute calculated from 30 s rhythm strip	Continuous (expected range, 60-120)

P wave duration	Interval from beginning to end of P wave in ms (measure of intra-atrial conduction delay)	Continuous (expected range, 70-126 ms)

QRS duration	Interval from beginning to end of the QRS waveform	Continuous (expected range, 72-160 ms)

PR interval	Interval from the beginning of the P wave to the beginning of the QRS complex measured in ms. PR interval > 200 ms indicates an abnormal delay of conduction (1^st ^degree AV block).	Continuous (expected range, 112-240 ms)

QRS amplitude	Height of QRS waveform in μV	Continuous (expected range, 500-1000 μV

T_PEAK _- T_END_	Interval from the peak of the T wave (or nadir in inverted T waves) to the end of the T wave in ms. Prolonged T_PEAK _-T_END _indicates heterogeneity of repolarization and risk for arrhythmia	Continuous (expected range, 112-240 ms)

**Table 3 T3:** Definitions of Universal Proportions

Criterion	Definition
Sensitivity	Proportion of those with acute rejection who are positive for the ECG criterion

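### The blinding statement does not allow for the QTc safety alert to transplant cardiologists, and the alert can reach the physician confirmation that is part of the rejection outcome

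*Protocol article*

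**What the plan says.** Five places in the protocol article bear on this.

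- **Design** (and the Abstract) labels the study "prospective, double-blind, multi-center descriptive research study".
- **Analysis of ECG monitoring data** applies blinding to the biopsy pathologists and to the treating clinicians, with no exception for either. For the latter it reads: "clinicians who provide medical care in the transplant clinics will be blinded from the QT interval monitoring data". The same paragraph blinds the ECG readers to clinical status and biopsy results.
- **Procedures** sets up a safety alert: "we will notify patients' transplant cardiologists within 48 h of the detection of any QTc interval exceeding the population 99th percentile", given as 470 ms for men and 480 ms for women.
- **Statistical analysis, Table 2** defines acute allograft rejection as "EMB category 1R or 2R or 3R with confirmation by treating physician". This variable is the dependent variable of the logistic regression and the reference for sensitivity, specificity and the predictive values.
- **Diagnosis of acute allograft rejection** describes weekly or biweekly biopsies for the first two to three months. It then says: "After that time, biopsies are performed less frequently, based on clinical judgment and risk of rejection".

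**The concern.** The alert value comes from the daily recordings to which the clinicians are said to be blinded. Both statements cannot be true, and nothing in the article reconciles them.

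The inconsistency matters because the alert goes to the clinical team, and that team has two roles in producing the outcome. It confirms rejection after the pathologist has graded the biopsy, and in the later months it decides whether to biopsy at all. If an alert makes either step more likely, patients with long QTc are verified and confirmed more readily than patients without, and the comparison of the ECG criterion with rejection is no longer independent. Primary aim 1 (sensitivity and specificity) is exposed. So is primary aim 2, because a biopsy prompted by an alert can shorten the measured days to rejection.

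**Working it through.** **1. The passages side by side**

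| Step | Who acts | Blinded according to the text? | Receives the alert? |
|---|---|---|---|
| Measuring QTc | Core laboratory reader | Yes, to clinical status and biopsy | Not applicable |
| Grading the biopsy | Site pathologist | Yes, to QT data | Not named as a recipient |
| Confirming rejection (Table 2) | Treating physician | Yes, as a clinic clinician | On the natural reading may have, as transplant cardiologist |
| Ordering biopsies after 2–3 months | Clinical judgment | Yes, as clinic clinicians | As above |

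The first two rows are intact. The path is open in the last two.

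**2. How often an alert would occur**

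The article gives no alert rate, so this is a check of materiality under assumptions. Formula: P(QTc > limit) = 1 − Φ((limit − mean)/SD), for a single recording, assuming normality.

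Inputs from Table 1:
- the prospective in-hospital study, "449 ± 2 ms without rejection; 517 ± 11 ms with rejection";
- the severe-rejection study, 437 ± 36 ms in survivors and 475 ± 57 ms in the sudden-death group.

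The index criterion adds 25 ms. Applying an SD of 36 or 57 ms to the means of 449 and 517 ms is an assumption, because it borrows the spread from a different study. Treating 437 ms as a level before any rise is also an assumption, because Table 1 does not say which recording that mean refers to.

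Worked example, men, mean 449, SD 36: (470 − 449)/36 = 0.58, so P = 28%. After the rise, 449 + 25 = 474 and (470 − 474)/36 = −0.11, so P = 54%.

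| Mean, SD (ms) | Men > 470 | Women > 480 |
|---|---|---|
| *Before a rise* | | |
| 437, 36 | 18% | 12% |
| 449, 36 | 28% | 20% |
| 449, 16.1 (if ± 2 is a standard error with n = 65: 2 × √65) | 10% | 3% |
| *After a 25 ms rise* | | |
| 462, 36 | 41% | 31% |
| 474, 36 | 54% | 43% |
| 474, 16.1 | 60% | 36% |
| *Mean during rejection* | | |
| 517, 36 | 90% | 85% |
| 517, 57 | 80% | 74% |
| *Severe rejection, sudden-death group* | | |
| 475, 57 | 54% | 47% |

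The shares are per recording. With daily recordings for six months, the chance of at least one alert per patient can only be higher. On every set of inputs, alerts are more frequent after a rise than before it.

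**3. What the confirmation step could do**

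This is an illustration with every value assumed. Let true sensitivity against the biopsy grade be 50%. Let all alerted positive grades be confirmed, and a fraction c of the non-alerted ones. With alert shares a₊ among criterion-positive and a₋ among criterion-negative rejections:

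apparent sensitivity = 0.5·[a₊ + (1 − a₊)c] / {0.5·[a₊ + (1 − a₊)c] + 0.5·[a₋ + (1 − a₋)c]}

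- a₊ = 0.41, a₋ = 0.18: c = 0.9 gives 0.941/(0.941 + 0.918) = 51%; c = 0.6 gives 0.764/(0.764 + 0.672) = 53%.
- a₊ = 0.90, a₋ = 0.10: c = 0.9 gives 0.990/(0.990 + 0.910) = 52%; c = 0.6 gives 0.960/(0.960 + 0.640) = 60%.
- c = 1 (confirmation ignores the alert): 50%, no bias.

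In the same illustration, with true specificity 80% and 30% of patients having a positive grade, apparent specificity is 78–79% in the first case and 80–81% in the second. The measures need not all move the same way. Alert-prompted biopsies are not modelled here.

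**The case against.** The strongest reply accepts the contradiction and disputes what follows from it.

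- **The index test is not disclosed.** A reader might infer that the ECG criterion feeds its own reference standard, which would be incorporation bias. The documents do not support that. The alert concerns one absolute value. The criterion is a rise of at least 25 ms over the previous day that lasts three days, and a patient can meet either without the other. QT is not a component of the rejection definition. What remains is possible review and verification bias through a correlated measurement.
- **The confirmer is not named.** No sentence says that the treating physician in Table 2 is the cardiologist who was alerted. It is the natural reading and nothing requires a different person, but it is an inference.
- **Real safeguards stand.** ECG readers and pathologists remain blinded. Routine early biopsies follow site surveillance protocols, so in general they do not depend on an alert.
- **Inflation is not established.** It is zero if alerts are ignored, and changes in care after an alert could work the other way.
- **Most true positives being unblinded is not established either.** The 74–90% figures join a mean from one study to SDs from another. A 25 ms rise from 449 ms with SD 36 gives 43% in women.

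All five points stand and they limit the wording. None of them reconciles the alert with the unqualified blinding statement or closes the path through confirmation and later biopsies.

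**Conclusion.** The blinding statement and the double-blind label are inaccurate as written, because the Procedures section discloses QTc values to clinicians who are said not to see them. That much follows from the text alone.

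The consequence for the primary outcome is an open path, not a demonstrated bias. It rests on the natural reading that an alerted cardiologist may also be the confirming physician, and on the article's statement that later biopsies follow clinical judgment. The likely direction is higher apparent sensitivity and a shorter interval to diagnosis. Neither direction nor size can be computed from the article.

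The path is not negligible. Under normal distributions with SD 36 ms, 12–28% of single recordings before a rise would trigger an alert, or as few as 3–10% if the ± 2 ms is a standard error. After a 25 ms rise or at the cited rejection mean, the share is 31–90%. These shares describe alert frequency only and are not a measure of bias.

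**What to change.** Leave the safety alert as it is. This point takes no position on its thresholds or on what clinicians do with it.

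1. **Reconcile the text.** In the Abstract, Design, Procedures and the blinding paragraph, state that treating clinicians are blinded to the QT monitoring data except for safety alerts, and qualify the double-blind label accordingly.
2. **Protect the outcome.** Use the blinded pathologist's biopsy grade as the outcome for the accuracy analysis and report the physician-confirmed version beside it. Alternatively, require that the person who confirms rejection has no access to alerts.
3. **Record and test.** Log the date of every alert. As a sensitivity analysis, repeat the accuracy and days-to-rejection analyses without biopsies and confirmations that follow an alert. Define in advance how long after an alert they count as following it, since repeated alerts could otherwise exclude much of the data.

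**Cost.** A few sentences and one date field; alert dates that are not logged may be hard to recover later. The grade-only outcome loses the clinical support that the article wants for Grade 2 readings, where Quilty lesions can mislead, which is why both versions should be reported. The sensitivity analysis removes alerted patients selectively, so it belongs beside the main result and does not replace it.

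Limiting the primary analysis to scheduled biopsies is not recommended. It would also drop unscheduled biopsies that no alert preceded, and it could remove much of the later part of the six-month period.

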Specificity	Proportion of those without rejection who are negative for the ECG criterion

Positive Predictive Value	Proportion of patients with positive ECG criterion who have rejection

Negative Predictive Value	Proportion of patients with negative ECG criterion who do not have rejection

Predictive Accuracy	$\frac{\#\text{true positives}\pm \text{true negatives by the ECG criterion}}{\text{Total }\#\text{ of patients enrolled in the study }\times \text{ 1}00}$

Descriptive statistics (means ± SD) will be used to describe the average time period between the development of the ECG criterion and biopsy evidence of rejection. In addition, we will report the proportion of subjects who develop the ECG criterion (≥ +25 ms increase in QT interval from previous day lasting 3 consecutive days [10]) before, during, or after the stages of mild, moderate, and severe rejection.

The Kaplan-Meier method with the log-rank test will be used to estimate survival curves over one year and to compare all-cause mortality in patients who are positive or negative for the QT_C _criterion. Cox Proportional Hazard modeling will be used to control for baseline differences between groups and for tacrolimus use.

Logistic regression will be used with the dependent variables of rejection (yes/no) and all- cause mortality (yes/no). In both regressions, tacrolimus dosage (with "0" entered if the patient is not receiving tacrolimus) will be included as a covariate in the model. If any of the explorative variables are statistically significant, a multiple logistic regression model will be used including the ECG criterion of interest to determine whether additional ECG criteria are independent predictors of rejection and death.

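### The ECG criterion measures change from the previous day's QTc, which its cited source cannot support and which a steady rise can escape; "persists" is also left undefined

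*Protocol article*

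**What the plan says.** The protocol article states the criterion in the Abstract, in Analysis of ECG monitoring data, and in Statistical analysis (text and Table 2). Under Analysis of ECG monitoring data, a QTc "interval from the previous day of at least 25 ms that persists for 3 consecutive days will be considered abnormal". Procedures shows that the comparator is intended: each patient is his or her own control, "noting any change from the previous day's QT interval". Table 2 repeats the rule and attaches the citation: "interval from previous day lasting 3 consecutive days [10".

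Table 1 (Background) describes reference [10], the 200-patient retrospective study. A rise of more than 25 ms in the QTc "interval predicted acute allograft rejection with sensitivity, 77%; specificity, 96" percent. The limitation listed beside it is "Only analyzed 2 ECGs per subject".

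The only mean QTc values with and without rejection come from the 65-patient prospective study in the same table: "449 ± 2 ms without rejection; 517 ± 11 ms with rejection".

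No section defines a stable per-patient baseline, or says which reading the second and third days are compared with.

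**The concern.** This one variable is the index test for both primary aims. It feeds sensitivity, specificity, the predictive values and the logistic regression. It also defines the groups in the secondary mortality comparison. Days to rejection in Table 2 count from the first positive criterion, so an early chance positive would also distort the timing results.

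Three things look wrong:

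- **Source.** Two ECGs per subject cannot show a rise from one day to the next that holds for 3 days. The published accuracy belongs to a different test.
- **Comparator.** With the previous day as reference, the reference climbs along with a gradual rise. The study seeks an early marker, so gradual prolongation matters.
- **Persistence.** The words allow two rules that behave very differently.

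If the study finds poor accuracy, the prespecified analysis would not separate an uninformative QTc from an unsuitable rule.

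**Working it through.** The article gives no operating characteristics for the day-to-day rule, so there is no stated figure to reproduce.

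**Inputs from the article.** Threshold 25 ms; 3 consecutive days; previous-day reference; daily recording for 6 months (taken as 180 readings); mean QTc 449 ms without and 517 ms with rejection.

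**Assumptions.** The day-to-day SD of QTc within a patient is not in the article, and the ± values in Table 1 cannot serve as one. It is varied over 3 to 12 ms, with independent normal errors. The speed of the rise is not given either; equal daily steps are assumed.

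**Step 1: steady rise without noise.** Total = 517 − 449 = 68 ms. Daily step = 68 / number of days:

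- 1 day: 68.0 ms
- 2 days: 34.0 ms
- 3 days: 22.7 ms
- 4 days: 17.0 ms
- 7 days: 9.7 ms

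From 3 days on, the step is below 25 ms. The limit depends on the total: 45 ms (10% of 449) already fails over 2 days (22.5 ms per day), while 100 ms fails only from 5 days (20 ms per day).

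**Step 2: two readings of persistence.**

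- *Single reference:* all 3 days are at least 25 ms above the one reading before them. One reading 25 ms too low, followed by three ordinary days, is positive.
- *Successive steps:* each of 3 days is at least 25 ms above its own previous day. This needs at least 3 × 25 = 75 ms, so 68 ms fails at any speed without noise. The single low reading is not positive.

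**Step 3: simulation of the single-reference reading** (20,000 patients per setting; false positives over 180 days with no true change; hits counted around the rise).

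| Assumed SD (ms) | Rejection-free patients ever positive | 68 ms rise over 7 days caught |
|---|---|---|
| 3 | 0% | 0% |
| 5 | 0.02–0.04% | 6% |
| 8 | 10% | 33% |
| 10 | 44% | 49–50% |
| 12 | 79–80% | 62–63% |

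Ranges show the spread between simulation runs. At the larger SDs, many of the hits come from the same noise that produces the false positives. Under the successive-steps reading, false positives are 0.7% or less up to SD 20 ms, and a 68 ms rise is caught at most about 3% of the time up to SD 15 ms.

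**Step 4: own-baseline comparator.** Take QTc minus a trailing 14-day median ending several days earlier, at least 25 ms on 3 consecutive recordings. It catches the 7-day rise about 100% of the time, with under 1% false positives up to SD 12 ms. The advantage narrows with more noise: a related version, using the mean of the first 7 days, gives 7.5% false positives at SD 15 ms and 28% at SD 20 ms.

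**The case against.** The comparator is deliberate. Procedures argues that comparing a patient with the day before keeps stable tacrolimus from interfering. Instrumentation, Procedures and the Discussion argue that the denervated graft varies little over 24 hours. If that is right, the low end of the SD range applies and false positives under the single-reference reading are negligible. That stands as a limit on the noise argument. It does not help detection, because at SD 3 to 5 ms the 7-day rise is caught only 0% to 6% of the time.

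A reader might infer that a rise taking 3 or more days can never qualify, however large. The documents do not support that. A rise of 30 + 20 + 18 ms qualifies under the single-reference reading without noise, and so does 100 ms over 3 days. With noise, a 68 ms rise over 3 days is flagged 62% of the time at SD 3 ms and about 86% at SD 10 ms. The 68 ms is also a difference of group means, not a within-patient change, and the article gives no time course; timing is what the second primary aim sets out to study.

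A reader might also infer that the rule both misses rises and fires on noise as established fact, or combine the 75 ms total with the low-reading false positives. Those two belong to different readings of persistence, and the noise figures depend on an SD that the article does not give.

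Finally, an own-baseline rule has weaknesses of its own. Under an assumed benign sustained shift of 15 ms at SD 10 ms, a fixed 14-day early baseline flags about 40% of rejection-free patients, not far below the previous-day rule's 49%. A trailing median flags about 4%, but misses a 68 ms rise spread over 42 days about half the time at SD 10 ms, and nearly always at SD 3 to 5 ms. This stands, and the fix must allow for it.

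**Conclusion.** The point holds in conditional form. The mismatch with reference [10] and the open meaning of persistence can be read from the article without any assumption. That a steady 68 ms rise over 3 or more days fails the rule follows by arithmetic, given equal steps, no noise and 68 ms as an illustrative size. The false-positive rates (about 0% to 79% over SD 3 to 12 ms) hold only under the single-reference reading and the assumed independent errors.

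It would go too far to say that the study could never tell a poor marker from a poor rule. Daily QTc values are measured and kept, so another baseline can be computed later. That analysis would, however, not be prespecified.

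Two related slips are clerical. Table 2 types the thresholded criterion as "Continuous (expected range, 10-100 ms", starting below its own 25 ms cut, while the regression uses presence or absence. The timing paragraph of Statistical analysis says "25 ms increase in QT interval from previous day lasting 3 consecutive days", without the heart-rate correction.

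**What to change.** Before QTc readings are linked to biopsy results:

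1. For the analysis, define delta-QTc as the day's QTc minus the patient's own baseline, for example a trailing 14-day median ending several days earlier. Call it positive when it is at least 25 ms on 3 consecutive recordings.
2. Keep the previous-day rule as a named secondary criterion, and state which reading each of the 3 days is compared with.
3. Report the alternative baseline (fixed early, if the trailing one is primary) as a sensitivity analysis.
4. Cite reference [10] only for the 25 ms size.
5. Use QTc in every statement of the criterion, and list the continuous delta-QTc and the yes/no criterion as separate variables in Table 2.

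The cost is wording in the Abstract, Procedures, Analysis of ECG monitoring data and Statistical analysis. No new data are needed, and the safety notification in Procedures, which uses absolute QTc limits, is untouched. The price is an initial run-in that cannot be evaluated, exposure of a fixed early baseline to drift unrelated to rejection (such as drug changes), and lower sensitivity of a trailing baseline to rises spread over many weeks.
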